## Abstract

**Background:**

The potential anti-cancer effects of mammalian target of rapamycin (mTOR) inhibitors are being intensively studied. To date, however, few randomised clinical trials (RCT) have been performed to demonstrate anti-neoplastic effects in the pure oncology setting, and at present, no oncology endpoint-directed RCT has been reported in the high-malignancy risk population of immunosuppressed transplant recipients. Interestingly, since mTOR inhibitors have both immunosuppressive and anti-cancer effects, they have the potential to simultaneously protect against immunologic graft loss and tumour development. Therefore, we designed a prospective RCT to determine if the mTOR inhibitor sirolimus can improve hepatocellular carcinoma (HCC)-free patient survival in liver transplant (LT) recipients with a pre-transplant diagnosis of HCC.

**Methods/Design:**

The study is an open-labelled, randomised, RCT comparing sirolimus-containing versus mTOR-inhibitor-free immunosuppression in patients undergoing LT for HCC. Patients with a histologically confirmed HCC diagnosis are randomised into 2 groups within 4-6 weeks after LT; one arm is maintained on a centre-specific mTOR-inhibitor-free immunosuppressive protocol and the second arm is maintained on a centre-specific mTOR-inhibitor-free immunosuppressive protocol for the first 4-6 weeks, at which time sirolimus is initiated. A 2^1/2^ -year recruitment phase is planned with a 5-year follow-up, testing HCC-free survival as the primary endpoint. Our hypothesis is that sirolimus use in the second arm of the study will improve HCC-free survival. The study is a non-commercial investigator-initiated trial (IIT) sponsored by the University Hospital Regensburg and is endorsed by the European Liver and Intestine Transplant Association; 13 countries within Europe, Canada and Australia are participating.

**Discussion:**

If our hypothesis is correct that mTOR inhibition can reduce HCC tumour growth while simultaneously providing immunosuppression to protect the liver allograft from rejection, patients should experience less post-transplant problems with HCC recurrence, and therefore could expect a longer and better quality of life. A positive outcome will likely change the standard of posttransplant immunosuppressive care for LT patients with HCC.

**Trial Register:**

Trial registered at http://www.clinicaltrials.gov: NCT00355862

(EudraCT Number: 2005-005362-36)

## Background

Patients with HCC that receive a LT in an attempt to cure their cancer and any superimposed liver disease face at least two major issues. First, the patient requires adequate immunosuppressive medication to avoid rejection of the liver allograft. Second, the patient has a risk that the HCC recurrence could recur, especially when in an immunosuppressed state. Even when restricting LT to patients with limited tumour expansion (e.g. Milan Criteria [1]), some HCCs recur. Furthermore, a significant number of pre-LT analyses of tumour extent are underestimated according to pathologic reports on explanted livers, leaving certain patients at a particularly high risk for HCC recurrence.

Adding to the problem of HCC recurrence, immunosuppressive agents used to prevent allograft rejection are generally regarded as tumourogenic, or at least permissive of cancer development. It is particularly notable that the most commonly used immunosuppressive class of compounds in LT patients, calcineurin inhibitors (cyclosporine and tacrolimus), have been implicated to support tumour formation. Cyclosporine has been shown *in vitro *to enhance cancer cell invasiveness [2] and support angiogenesis accompanying tumours [3,4]. It has also been reported that cyclosporine inhibits DNA repair mechanisms [5], potentially promoting tumour development. Regarding LT, cyclosporine has been shown to promote liver tumour growth and recurrence in an experimental rat model [6]. In other experimental studies, a higher proliferation rate of human hepatoma cells could be demonstrated in the presence of another calcineurin inhibitor, tacrolimus [7]. It remains, however, unproven whether calcineurin inhibitors actually result in a higher HCC recurrence in the setting of LT.

A new view towards this "old problem" of HCC recurrence is supported by recent studies showing that one class of immunosuppressants, mTOR inhibitors, is capable of not only inhibiting immune responses against transplanted allografts, they may also be potent antineoplastic agents. Rapamycin, as the first described mTOR inhibitor, has strong antiangiogenetic effects that inhibit tumour growth in numerous experimental models [3,4,8]. Indirect inhibition of tumor metastasis has also been reportedly due to increased E-cadherin expression on tumour cells [9]. Not only does rapamycin inhibit tumour growth indirectly, cancer cells themselves are inhibited directly by their variable dependence on the mTOR pathway for cell growth and survival [10]. Interestingly, HCC tends to be highly vascularised [11], suggesting a potential susceptibility to rapamycin. Moreover, experimental models indicate that the mTOR signalling pathway is utilised by hepatic tumour cells [12].

From a clinical perspective, mTOR inhibitors have begun to show efficacy with some types of cancer, including especially advanced renal cell carcinoma [13,14]. Little information is available in the context of organ transplantation. While early indications from transplant registry data [15], and from studies not directed at determining tumour development, suggest a general decrease in cancer with mTOR inhibitors, no prospective randomised data has yet confirmed this idea. Most data published with respect to tumour development in transplant recipients has been with the mTOR inhibitor, sirolimus. Although not powered for an oncologic endpoint, studies using sirolimus suggest skin cancer, and other malignancies may be fewer in transplant recipients [16]. Small non-randomised uncontrolled pilot trials and retrospective analyses also hint that sirolimus may improve the outcome for LT patients with a pretransplant diagnosis of HCC [17,18], regarding both tumour recurrence and a more benign course of renewed HCC disease [19]. Unfortunately, these ostensible effects can only be confirmed in a controlled prospective randomised clinical trial.

Based on these experimental and clinical observations, we have designed a clinical trial protocol with the purpose of testing whether the mTOR inhibitor sirolimus can improve HCC-free survival after LT. We predict that patients treated with sirolimus will experience an improved HCC-free survival.

## Methods/Design

### Basic protocol overview

This is an open-labeled, randomised, prospective multi-center clinical trial comparing sirolimus-containing versus mTOR-inhibitor-free immunosuppression in patients undergoing LT for HCC. We have named the trial the "SiLVER Study", referring to the use of sirolimus in LT patients with HCC. The study is planned for 8 years in total, consisting of a 3-year enrolment period and a 5-year follow-up. Patients with a histologically proven HCC either within Milan Criteria or with extended criteria will be randomised into 2 groups between day 22 and 42 (inclusive) after LT. The first group will be maintained on a centre-specific mTOR-inhibitor-free immunosuppressive protocol. This control arm will be compared to a second group of patients that will be treated with the centre-specific protocol for the first 4-6 weeks, at which time sirolimus will be incorporated (between day 29 and day 42) into the regime either as a monotherapy, or as a combination therapy with non-mTOR-inhibitor-based immunosuppression (Figure 1).

**Figure 1 F1:**
[figure not shown]
**Inclusion and Randomisation Scheme**.

Notably, HCC staging will be assessed in the explanted liver to determine the actual extent of tumor presence. This information will be used with the pre-LT data to determine if the patient is to be stratified into a high or low risk group, based primarily on fulfilment of Milan Criteria.

### Inclusion criteria

The study includes all patients eligible for LT as outlined by each of the participating centres, including deceased whole-allograft and split-liver donors, as well as living donors.

General inclusion criteria are: age over 18 years, histologically proven HCC before randomisation and signed, written informed consent given by the patient. Individual patients who were treated pre-LT for histologically proven HCC, for example by chemoembolisation, radiofrequency ablation, or percutaneous ethanol instillation, may show tumour reduction, or even complete necrosis, after posttransplant histological staging in the explanted liver. If there is complete tumour necrosis, histological confirmation of HCC post-LT will not be possible. In these cases, patients with a pretransplant histological diagnosis of HCC may still be included in the study. However, complete biological tumour response patients will be down-staged and therefore stratified into the group considered within Milan criteria. In all patients with a pre-LT histological proof of HCC, and an incomplete tumour response following pretreatment, stratification will be solely performed according to the final postoperative histology. For example, in the case of pre-LT diagnosis of an HCC outside the Milan criteria, and subsequent post-LT pathology revealing reduced tumour extent within the Milan criteria, final stratification will be performed according to the post-LT histology report.

### Exclusion criteria

Patients with extrahepatic non-HCC malignancies within the past 5 years (excluding successfully treated squamous cell carcinoma and basal cell carcinoma of the skin) will be excluded. Multiple-organ recipients, patients with a known hypersensitivity to sirolimus or its derivates, hyperlipidemia refractory to medical management, evidence of local or systemic infection, HIV, platelets <75,000/nl, women of child-bearing potential not willing to take contraception, patients with extrahepatic HCC tumour manifestation, and patients with a psychological, familial, sociologic or geographic condition potentially hampering compliance with the study protocol and follow-up schedule or under guardianship (e.g. individuals who are not able to freely give their informed consent), and patients receiving mTOR inhibitors prior to day 29 after LT will also be excluded.

### Study objectives

Our hypothesis is that sirolimus use in the test arm of the study will improve HCC-free survival in this LT population. The primary endpoint in this trial is HCC recurrence-free patient survival with sirolimus-containing versus mTOR-inhibitor-free immunosuppression in patients undergoing LT for HCC. Secondary endpoints will be patient overall survival, incidence of *de novo *malignancies, liver allograft and kidney function, HCV and HBV recurrence, time to HCC recurrence, tumour number and size at the time of recurrence, tumour progression rate, and HCC-free, as well as, overall -survival in high and low -risk groups.

### Randomisation and treatment scheme

Patients will be randomised via an interactive voice response system (IVRS) into one of the two treatment arms after histologically proven HCC. After the patient is assigned to a treatment group, a code to uniquely identify the patient (Patient ID) and the assigned treatment group is transmitted via fax. In treatment arm 1, patients are treated with the centre-specific immunosuppressive protocol, excluding the use of any mTOR-inhibitor medications. Steroid reduction is encouraged by 3 months post-LT. In treatment arm 2, application of sirolimus is started between day 29 and 42 after LT with a loading dose of 5 mg/d, and 2 mg/d thereafter. The first sirolimus trough level is measured after 3 to 4 days, followed by trough levels once a week for 4 weeks and twice a month thereafter. The desired trough level for sirolimus is 4-10 ng/ml. Simultaneously, the use of mycophenolic acid prodrugs (mycophenolate mofetil, Roche; enteric-coated mycophenolate sodium, Novartis) and of calcineurin inhibitors should be reduced by 50%. Steroid reduction by 3 months is encouraged. The ideal long term, but not obligate, goal is sirolimus mono-therapy in arm 2.

### Follow-up and documentation

In the first year after LT all patients will be followed-up after month 1, 3, 6, 9 and 12. Thereafter, patients are followed-up every 6 months. Sirolimus levels in patients within arm 2 will be tested and adjusted if need be at each follow-up date.

In general, regular documentation includes data on graft survival, graft dunction as measured by laboratory values, incidence of clinically-diagnosed and biopsy proven acute graft rejection, severity of rejection (histological grade), incidence of premature withdrawal from study medication for any reason, changes in glucose or lipid metabolism, renal function, changes in systolic and/or diastolic blood pressure, adverse events, infectious complications, wound-healing disturbances, haematological toxicity, gastrointestinal side-effects, thrombembolic complications, tumour recurrence information and patient survival.

If a patient should miss two consecutive follow-up visits and the investigator cannot establish contact with the patient, the status of the patient will be set to 'lost-to-follow-up'. If the last contact was prior to the diagnosis of a recurrence event, recurrence-free survival time will be censored using the date of the last contact. If contact with the patient can be re-established, the status for survival time will be reset to alive. However, recurrence-free survival time and accompanying censoring status will remain. If the date of a patient's death is documented, the status will be "dead".

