### Endpoint definition

HCC recurrence-free survival (RFS) is specifically defined as the time interval between the date of LT and the date of HCC recurrence or death (as first event); patients who are alive and recurrence-free at the time of analysis will be censored for RFS at the time of their last contact. HCC recurrence is defined as either histologically-proven tumour recurrence, or unequivocal tumor recurrence determined by the Barcelona Criteria (Barcelona-2000 EASL Conference). Date of recurrence is defined as the first day of tumor suspicion. Clinical evidence for HCC recurrence including β-symptoms, weight loss, inappetence, pruritis, and ascites are considered suspicious signs and are followed up by definitive diagnostic action in accordance with the Barcelona Criteria. Recurrence of HCC can therefore be determined during the entire follow-up period, and not only at protocol-assigned visits.

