### Sample size

Sample size was calculated using the primary endpoint of RFS assuming proportional hazards and exponential distributions of RFS. RFS time distributions of combined high and low risk patients in the two treatment groups will be compared using a two-sided (stratified) log-rank test at a 0.05 significance level. A 5-year RFS rate of 60% (or equivalently an event rate of 40%) in patients treated with mTOR-inhibitor-free immunosuppression is expected. An increase to a 5-year RFS rate of 72% (or equivalently a decrease to an event rate of 28%) due to sirolimus-containing immunosuppression is assumed. The improvement in 5-year RFS rate from 60% to 72% (or equivalently a decrease in 5-year recurrence event rate from 40% to 28%) corresponds to a hazard ratio of 0.643 and is considered as clinically relevant. For detecting a HR of 0.643 with a power of 1-β = 0.80 in the three-stage group sequential design with an α spending function of the O'Brien and Fleming type, it is necessary to observe 164 events (HCC recurrences or deaths). Assuming an accrual time of 2 1/2 years and a follow-up time of at least 5 years from the last patient recruited, a total of 405 patients are expected to yield the necessary number of events. With a lost to follow-up rate of about 20%, a total of 510 patients (255 per treatment group) are required.

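### After re-contact, the loss-to-follow-up rule keeps RFS censored, so a recurrence found later is censored there but is an event under the endpoint definition

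*Protocol article*

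**What the plan says.** All references are to the protocol article.

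**Follow-up and documentation.** The rule starts with "If a patient should miss two consecutive follow-up visits and the investigator cannot establish contact with the patient"; the patient is then classed as lost to follow-up. Where no recurrence had been diagnosed by then, RFS is censored on the day the patient was last in touch. If the patient resurfaces, two things happen. For overall survival, "If contact with the patient can be re-established, the status for survival time will be reset to alive". For the primary endpoint, "However, recurrence-free survival time and accompanying censoring status will remain". No exception is made for a recurrence found afterwards. A closing sentence sets the status to dead once a date of death is documented, without saying whether this means the survival status, the RFS status or both.

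**Endpoint definition.** RFS runs from transplantation to recurrence or death, whichever is first, and "patients who are alive and recurrence-free at the time of analysis will be censored for RFS at the time of their last contact". The section adds that recurrence can be established at any time in follow-up, not only at scheduled visits.

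**Statistical evaluation** makes the intention-to-treat set primary and uses a (stratified) log-rank test. **Sample size** allows for loss: "With a lost to follow-up rate of about 20" per cent, 510 patients are required.

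**The concern.** The two sections give different answers for the same patient. Someone who is silent for two visits, is found again and has a confirmed recurrence is an event by the endpoint definition and a censored observation by the follow-up rule. Someone found alive and recurrence-free is censored at the new contact by one rule and at the old contact by the other.

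This is a conflict between two stated rules for the primary endpoint, not a detail left to an analysis plan. It leaves the analyst to choose between derivations, in an open-label trial, possibly after outcomes are known. Under the freezing rule, outcomes the trial holds are set aside. The log-rank test and Kaplan-Meier curves assume that censoring is unrelated to prognosis. Patients who go silent may not meet that assumption, and here the censoring is kept by rule even when the missing information has arrived.

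**Working it through.** **1. The rules side by side, for a patient declared lost**

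| What is later learned | Follow-up and documentation | Endpoint definition |
|---|---|---|
| Found, recurrence documented | RFS censored at old last contact | Event |
| Found, alive and recurrence-free | RFS censored at old last contact | Censored at latest contact |
| Death documented, no prior recurrence | Status dead; effect on RFS not stated | Event |
| Never found, nothing learned | Censored at last contact | Censored at last contact |

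The first two rows conflict outright. The third is unclear. The fourth does not differ, so the issue concerns only lost patients about whom something is later learned.

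**2. The plan's own figures reproduce**

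- HR = ln(0.72)/ln(0.60) = 0.643.
- 164 events with looks at 55, 109 and 164, using Lan-DeMets O'Brien-Fleming-type bounds (z = 3.698, 2.516, 1.993), give power 0.802.
- Hazards per year: control −ln(0.60)/5 = 0.1022; sirolimus −ln(0.72)/5 = 0.0657.
- With uniform accrual over 2.5 years and at least 5 years of follow-up, the event probabilities are 0.4705 and 0.3360, mean 0.4033. Then 164/0.4033 = 407, against 405 stated.
- 405/0.80 = 506.25, so 507, against 510 stated.

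There is no arithmetic error in the sample size.

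**3. How many known events the freeze could drop**

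Assumptions, not in the document: loss is exponential and unrelated to outcome, with 20% lost by year 5, so ν = −ln(0.80)/5 = 0.0446; 510 patients are counted to calendar end. With λ the arm's hazard and m = λ + ν,

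P(event before loss) = (λ/m) × [1 − (e^(−5m) − e^(−7.5m))/(2.5m)].

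- With loss: 0.4163 control, 0.2957 sirolimus, mean 0.3560; × 510 = 181.6 events.
- Without loss: 0.4033 × 510 = 205.7 events.
- First events falling after loss: 205.7 − 181.6 = 24.1.

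| Share of post-loss events that become known | Dropped (20% lost by year 5) | Dropped (20% lost by year 7.5) |
|---|---|---|
| 10% | 2.4 | 1.7 |
| 25% | 6.0 | 4.1 |
| 50% | 12.0 | 8.3 |
| 100% | 24.1 | 16.5 |

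These are upper figures for two reasons. They count deaths as well as recurrences, and deaths may already count under the ambiguous sentence. They also run to calendar end, whereas the final analysis is planned at 164 events.

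**4. Whether the HR moves**

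Large simulation of the same model, multiplying the hazard after loss as shown (illustrative; none of these multipliers is in the document):

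| Hazard after loss | Frozen rule | Updated, 25% found | Updated, 50% found | Updated, 100% found |
|---|---|---|---|---|
| Unchanged | 0.64 | 0.64 | 0.64 | 0.64 |
| Doubled in both arms | 0.64 | 0.65 | 0.65 | 0.65 |
| Doubled, sirolimus only | 0.64 | 0.66 | 0.68 | 0.71 |
| Doubled, control only | 0.64 | 0.62 | 0.61 | 0.58 |

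A worse prognosis after loss that is shared by both arms leaves the HR essentially where it was. A difference between arms is needed to move it, and it can move either way.

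**5. Event target**

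Under the frozen rule about 182 to 189 events are still expected before loss, so 164 is reached. Power counted to calendar end is about 0.84 to 0.85 with no post-loss events, and 0.88 with all of them.

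**The case against.** **Freezing has a rationale.** It is prespecified, treats both arms alike and avoids crediting recurrence-free time nobody observed. A careless update would also do harm: if patients resurface because something has happened to them, while event-free patients stay censored at the old date, ascertainment is event-driven. In the model above, if only patients with events return, 5-year control RFS falls from 60% to about 57% when all of them return and about 59% when half do. This stands as a constraint on the fix. It does not justify a rule that contradicts the endpoint definition.

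Four stronger readings are tempting and are not supported.

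- *Known deaths are discarded.* The freezing sentence suggests it, but the next one reads "If the date of a patient's death is documented, the status will be 'dead" and does not restrict which status is meant, while the endpoint definition counts death as an event. The natural reading is survival status, since that is the status just discussed, but the text does not settle it.
- *The trial will lose 24 events.* That needs every lost patient to be found. The 20% is a loss rate; no re-contact rate is given.
- *The primary HR is biased, for example 0.64 reported where 0.71 is true.* That needs full re-contact and a change in hazard in one arm only. Nothing in the document supports either.
- *Intention-to-treat is broken.* Lost patients remain in the analysis set, in their randomised arm, up to the censoring date. What is lost is later outcome information on them.

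**Conclusion.** The contradiction is real and concerns the primary endpoint. A recurrence documented after re-contact is censored under Follow-up and documentation and is an event under Endpoint definition. The treatment of deaths is ambiguous rather than wrong.

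In number, the effect runs from about 2 known events (10% re-contact) through 6 and 12 (25% and 50%) to a ceiling of 24, given the design hazards and 20% exponential loss by year 5. The true figure cannot be derived, because the re-contact rate is not stated. Bias in the HR arises only if outcome after loss, or the chance of being found, differs by arm; its size and direction cannot be computed from the document. Nothing here changes the 164 events or the 510 patients.

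**What to change.** Reconcile the two sections by replacing the sentence that freezes RFS:

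1. On re-contact, RFS is updated for every patient by the endpoint definition. A documented recurrence or death is an event on its date; otherwise the patient is censored at the latest date known to be alive and recurrence-free.
2. State that a documented death counts for RFS as well as for overall survival.
3. Before each interim and final analysis, seek and update the status of lost patients in the same way in both arms and regardless of event status, so that ascertainment is not driven by events.
4. Keep the frozen-censoring rule as a sensitivity analysis.

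The cost is a few sentences, the endpoint derivation program and a status sweep before each analysis. It is not entirely free of new data: recurrence status must be recorded at re-contact, and recurrence dates that fall within the gap in follow-up will be less certain than those seen at regular visits.
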